**Fig. 1 Fig1:**
[figure not shown]
schematic representation of the study trial at each treatment location

### Study population

Patients are eligible for participation in the current trial, if they meet the following inclusion criteria: (1) an age of 16 years or older; (2) the ability to read and speak the Dutch language; (3) a DSM-5 classification of anorexia nervosa (AN), bulimia nervosa (BN), or other specified feeding and eating disorder (OSFED) that identifies as an atypical AN or BN variant with a low frequency or limited duration of binges / purges and (4) failure to show an early response after 8 sessions CBT-E. The Jacobson-Truax Reliable Change Index (RCI) approach will be used to assess whether the early CBT-E response is significant or not [35]. Exclusion criteria include: (5) the presence of an acute psychosis; (6) a clinically diagnosed autism spectrum disorder (ASD); (7) currently receiving schema therapy elsewhere and (8) an IQ below 80.

### Setting and recruitment of participants

Patients will be recruited from ED treatment centers in The Netherlands including GGnet Amarum (Warnsveld, Nijmegen), GGz Breburg (Tilburg, Breda), Co-eur (Hoensbroek, Maastricht, Roermond, Utrecht, Vught), GGZ Friesland (Leeuwarden), and Accare (Groningen). Patients meeting the eligibility criteria will receive an invitation from their therapist for study participation. After receiving written and oral information about the study from the researchers, each patient will decide individually on study participation. Once active consent has been provided, the patient will be included in the study trial, after which phase 1 CBT-E will start.

### Sample size

In order to reliably measure the quantitative primary outcomes following completion of the GST treatment and continued CBT-E treatment, a two-tailed alpha of 5%, a power of 90% and a medium effect size of d = 0.50 is assumed. This yields a sample size of 86 patients per treatment arm, thus *N* = 172 in total for a classical RCT. However, there is clustering in the GST arm due to its group format for treatment delivery. Therefore, an additional design effect is needed to correct the GST sample size for potential clustering. Assuming a group size of 8 participants and an intra-class correlation of 0.10, a design effect of 1.70 was computed. When multiplying this design effect with the original sample size of the GST arm (*N* = 86), the adjusted necessary sample size for the GST arm is equal to 1.70 *86 = 146 participants. Adding the initial number of participants in the continued CBT-E arm (*N* = 86), the total number of necessary study participants is equal to *N* = 232.

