**Methods:**

Using a multicenter RCT design, 232 Dutch (atypical) AN and BN patients with a CBT-E referral will be recruited from five treatment centers. Clinical effectiveness and cost-effectiveness will be measured before treatment, directly after treatment, at 6 and at 12 months follow-up. In order to rate process evaluation, patient experiences and the degree to which treatments are implemented according to protocol will be measured. In order to assess the quality of life and the achievement of personalized goals, interviews will be conducted at the end of treatment. Data will be analyzed, using a regression-based approach to mixed modelling, multivariate sensitivity analyses and coding trees for qualitative data. We hypothesize GST to be superior to CBT-E in terms of clinical effectiveness and cost-effectiveness for patients who do not show a rapid response to the first 4 weeks of a CBT-E treatment.

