## Background

Eating disorders (EDs) are associated with decreased social, psychological, and physical functioning in individuals [1] and elevated premature mortality rates [2]. On a healthcare system level, EDs contribute substantially to the mental health burden. Between 2000 and 2018, the weighted mean of point ED prevalence across continents had increased from 3.5 to 7.8% [3].

In a similar vein, the collective ED disease burden is reflected through major socioeconomic constraints. On average, ED patients generate more healthcare expenses and have lower employment rates than people without ED [4]. According to Van Hoeken and Hoek [5], over 3.3 million healthy life years are lost worldwide annually due to EDs. In addition to that, these authors showed that ED patients generated a 48% increase in healthcare costs, compared to the general population, while EDs with comorbid other psychiatric disorders were associated with a 48% decrease in yearly earnings in those employed.

In clinical practice, enhanced cognitive behavioral therapy (CBT-E) is used as treatment for all types of EDs, because of its transdiagnostic applicability and effectiveness [6]. Even though CBT-E is clinically effective for a certain group of ED patients, it is presumably not the most clinically optimized treatment for patients with (atypical) Anorexia Nervosa (AN) or Bulimia Nervosa (BN). More specifically, CBT-E is characterized by a substantial dropout rate: 20–54% in randomized controlled trials [6], especially in AN [7–9]. In general, only 30–50% of ED patients achieve clinical remission after CBT-E treatment [6, 10].

Although certain ED patients are greatly capable of challenging their own belief systems during treatment, they are generally unable to modify deeply held core beliefs [11]. In line with this observation, many ED cases reflect a complex intertwining between eating pathology and comorbid personality pathology [11–13], including clinical perfectionism [14]. Moreover, comorbid personality pathology increases the risk of attrition and is associated with greater psychopathology after treatment [11]. Albeit uncertain, not all (atypical) AN and BN patients may benefit sufficiently from CBT-E, perhaps due to a lack of emphasis on deeply rooted core beliefs.

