#### Randomization

Random allocation to the control group (continued CBT-E) or the intervention group (GST) will be conducted separately for each treatment location in a ratio of 1:2 by an automatized randomization software program after the completion of the post measurement. This ratio is due to the cluster effect in group-based therapy, which statistically requires more participants for the GST arm than for the continued CBT-E arm. Subsequent to randomization, participants in the GST arm and continued CBT-E arm will complete a baseline measurement (T0). After that, both treatments will start. Post-measurements (T1) will take place on the known end date of the treatment to which a participant is randomized. Follow-up measurements will take place 6 months (T2) and 12 months (T3) later, following initial completion of the entire treatment trajectory at T1. Several clinical measurement instruments are used, see Fig. 1. The current study protocol has been approved by the Medical Research Ethics Committee (MREC) Academic Hospital Maastricht/University Maastricht in The Netherlands, which was formally registered as: NL80491.068.22. The study is registered at ClinicalTrials.gov (registration number NCT05812950), and complies with the World Health Organization Trial Registration Data Set. Modifications to the protocol will be submitted as an amendment and will be examined by the MREC and will be adjusted in the trial registry.

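### The stated 90% power holds only if all 232 randomised patients provide the primary outcome; nothing is allowed for loss, although the protocol itself expects dropout and incomplete data

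*Protocol article*

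**What the plan says.** The Sample size section gives a complete derivation. It sets "a two-tailed alpha of 5%, a power of 90% and a medium effect size", specifically "a medium effect size of d = 0.50 is assumed". The next step is "This yields a sample size of 86 patients per treatment arm". For the group format, "Assuming a group size of 8 participants and an intra-class correlation of 0.10, a design effect of 1.70 was computed", so that "the adjusted necessary sample size for the GST arm is equal to 1.70 *86 = 146 participants". Adding the 86 CBT-E patients gives 232. No step concerns dropout or missing outcomes.

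Other sections bear on this figure:

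- The Background states that "CBT-E is characterized by a substantial dropout rate: 20–54% in randomized controlled trials". It adds that patients without an early response may be at higher risk of dropping out, and these are the patients who are randomised.
- The Operational challenges section acknowledges a risk of incomplete data, notes that a full measurement can take up to two hours, and relies on intention-to-treat analysis as the answer.
- The Randomization section says that allocation "will be conducted separately for each treatment location in a ratio of 1:2" (CBT-E to GST).
- The abstract says that "232 Dutch (atypical) AN and BN patients with a CBT-E referral will be recruited from five treatment centers". The section on setting and recruitment includes patients at consent, before the first 8 CBT-E sessions, and the Design section removes early responders before randomisation.

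**The concern.** The number that the calculation requires in the two arms is the same number that the abstract plans to recruit. There is therefore no margin between patients needed for analysis and patients entered, in a population in which the article itself anticipates dropout. Intention-to-treat analysis keeps patients in their allocated arm; it does not restore the information lost when an outcome is not observed.

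The 90% is the figure against which a null result in this superiority trial will be read. If realistic completeness gives power in the low 80s, a non-significant result carries less weight against d = 0.50 than the article implies.

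Two further statements do not fit the derivation. An allocation of 1:2 does not produce 86 and 146, which stand at 1:1.70. And 232 patients recruited before phase 1 cannot be 232 randomised unless nobody responds early and nobody leaves.

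**Working it through.** **Inputs.** From the Sample size section: two-sided alpha 0.05, d = 0.50 (SD = 1), group size 8, ICC 0.10, arms 86 and 146. From the Randomization section: 1:2. From the Background: 20–54% dropout.

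**Reproducing the stated figure.** A two-sample t-test (noncentral t) has 89.99% power at 85 per arm and 90.3% at 86, so 86 is correct. Design effect: 1 + (8 − 1) × 0.10 = 1.70. GST arm: 1.70 × 86 = 146.2, stated as 146. Total: 86 + 146 = 232.

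**Power formula.** Clustering applies to GST only, so SE = √(1/n_C + DE/n_G), and power ≈ Φ(0.5/SE − 1.96). The percentages below use the noncentral t with n_G/DE as the effective GST size, which runs up to about one point lower.

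- 86:146, no loss: SE = √(1/86 + 1.70/146) = 0.1526; Φ(3.28 − 1.96) = 90.6%; noncentral t 90.3%.
- 77:155, no loss (232/3 = 77.3 and 154.7): SE = √(1/77 + 1.70/155) = 0.1548; Φ(3.23 − 1.96) = 89.8%; noncentral t 89.5%.
- 86:146 with 20% loss in both arms leaves 68.8 and 116.8. With DE held at 1.70, SE = 0.1706 and power is 82.9%. If groups shrink to 8 × 0.8 = 6.4, DE = 1 + 5.4 × 0.10 = 1.54, SE = 0.1665 and power is 84.7%.

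**Power over a range of losses.** Loss means missing EDE-Q. In the rows for loss in both arms, the first figure holds DE at 1.70 and the second lets it shrink with group size.

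| Loss | 86:146 | 77:155 |
|---|---|---|
| None | 90.3% | 89.5% |
| 2%, both arms | 89.7–89.9% | 88.9–89.0% |
| 20%, both arms | 82.9–84.7% | 81.8–83.5% |
| 30%, both arms | 77.6–80.6% | 76.4–79.2% |
| 54%, both arms | 59.3–65.3% | 58.0–63.5% |
| 20%, CBT-E only | 86.7% | 85.4% |
| 54%, CBT-E only | 73.3% | 70.7% |

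By the normal approximation with DE 1.70, 86:146 crosses 90% at a loss of about 2.2%; by the noncentral t it is already just below 90% at 2%. For scale, simple inflation for 20% loss would be 232/0.80 = 290 patients.

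**Allocation.** At 1:2 the CBT-E arm is 86 − 77 = 9 short of its stated size, but the larger GST arm offsets nearly all of this: 90.3% falls to 89.5%. By the normal approximation, 1:2 needs a total of about 233–234 for 90%, so there is no need to hold 86 in CBT-E (which at 1:2 would mean 3 × 86 = 258).

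**Baseline adjustment.** With the pre-treatment EDE-Q as a covariate, residual variance is multiplied by 1 − r². At an assumed r = 0.5 this is 0.75, the effective d is 0.5/√0.75 = 0.577, and power at 77:155 with 20% loss is 91.2–92.3%. For a simple change score the factor is 2(1 − r), which at r = 0.5 equals 1: no gain. The documents give no value of r.

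**The case against.** The strongest reply is that the 20–54% is not the trial's rate of missing EDE-Q. It is treatment dropout in CBT-E trials. Here patients leave the study only at their own request, analysis is by allocated arm whatever treatment was received, T1 is tied to the known end date of treatment, questionnaires are online, and on-site help is offered where possible. GST is expected to reduce dropout, and any dropout in the first 8 sessions comes before randomisation. All of this stands. It means the size of the shortfall cannot be fixed from the documents, and that 54% missing in both arms is an extreme case. It does not remove the point, because the calculation assumes no loss at all and every loss scenario tabulated lies below 90%.

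A second reply is that adjustment for baseline could recover the power. It could, but the Sample size section takes no such credit, and the Data analysis section speaks of change scores within mixed models, so the gain depends on the model and on an unstated correlation.

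A third is that an article condenses a fuller protocol. Here, though, the article prints the whole derivation and uses its result as the recruitment number, so no inflation step between the two is left for another document to supply.

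A reader might also infer more than the documents support:

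- *That 1:2 allocation is what loses the power.* It costs under one point.
- *That power is about 70–82% because only non-responders among 232 recruited would be randomised.* Those figures need a responder rate of 20–40%, which appears nowhere in the article, and a reading of 232 that the Sample size section contradicts, since it places 232 in the two arms. The abstract's wording is loose; it does not show that fewer than 232 will be randomised.

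**Conclusion.** The concern stands in limited form, as something that should be fixed. The arithmetic behind 232 is right, but the 90% is conditional on complete primary-outcome data from 86 and 146 patients, and the article does not say so while giving its own reasons to expect loss. Under d = 0.50, ICC 0.10, no covariate credit, and the assumption that treatment dropout becomes missing EDE-Q, power is about 82–85% at 20% loss in both arms and about 85–87% if only CBT-E loses 20%. The 58–65% at 54% loss in both arms marks the far end and is not a forecast.

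The conflict between the abstract and recruitment section (patients entered before phase 1) and the Sample size section (randomised arms), and that between 1:2 and 1:1.70, are real inconsistencies that need reconciling. Neither is the source of the power shortfall.

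**What to change.** No additional enrolment is required.

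1. Replace the unconditional 90% with the power at the expected T1 completeness of the EDE-Q, and show it for a range of losses as in the table above. Credit baseline adjustment only if the primary model includes the pre-treatment EDE-Q as a covariate and the assumed correlation is stated. By Table 1, the last EDE-Q before T1 is the one taken after the 8 sessions.
2. State that 232 is the number randomised, and correct the abstract, which describes patients recruited at referral.
3. As a minor reconciliation, restate the arm sizes as about 77 and 155 under the 1:2 allocation, with 89.5% power before any loss. Changing the randomisation ratio is unnecessary for a difference of under one point.

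The cost is a few sentences and a short table. The downside is that the stated power becomes less favourable.

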In light of the findings above, schema therapy (ST) may be a clinically effective alternative that offers potential for addressing comorbid personality pathology. In short, ST provides an integrative approach that is fundamentally geared towards treating people with deeply entrenched self-identity difficulties and interpersonal problems, which are reflected through maladaptive schemas and schema modes [15]. Using these theoretical foundations, ST is either delivered individually or in a group setting (GST) in clinical practice. While individual ST [16, 17] and GST [18] were already found to be clinically effective and cost-effective for treating personality disorders, the rationale underlying their application for effectively treating EDs has also been documented [19]. The hypothesis is that EDs are characterized by overdeveloped coping modes that either avoid schema activation or manage affect when schemas are triggered. In general, the theoretical foundations regarding schemas and schema modes have already been applied to eating disorders in certain pilot studies, which were considered promising [20–22]. Contrary to individual ST, GST aims to establish a collective sense of awareness among ED patients regarding their shared emotional needs and applied schemas and coping mechanisms, building upon therapeutic alliance in the context of a supportive group environment. As a result, the GST approach may prevent drop-out rates among ED patients [23], which is a major hurdle in current CBT-E delivery formats.

New studies with adequate control groups are needed in order to expand the preliminary body of evidence on GST for eating disorders. This is important, since current CBT-E does not automatically address personality pathology in patients with persisting EDs, leaving many of them without adequate potential for recovery [8, 24]. In general, (atypical) AN and BN patients not showing an early treatment response after the first 4 weeks of a CBT-E treatment may be at an elevated risk of dropping out and achieving suboptimal clinical outcomes after a full CBT-E trajectory [25–27]. Therefore, the current study protocol will focus on ED patients who do not show a significant reduction in ED symptoms after the first 4 weeks (8 sessions) of CBT-E, which is the first of four CBT-E treatment phases [28].

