### Operational challenges

Although we are confident about the general applicability and resilience of the current study protocol, there are certain operational challenges that require our consideration.

First, ED patients are at risk of comorbid physical and mental health complications [65]. Even though severely vulnerable and ill-protected ED patients will be excluded during the screening phase, we cannot rule out the possibility of ED patients terminating their research participation due to health complications in a subsequent research phase. As a result, there is an inherent risk of incomplete data, which we aim to address by conducting all statistical analyses according to the intention-to-treat principles. Additionally, information leaflets are tailored to the research treatment phases that apply to participating patients, supporting their treatment adherence.

Second, participating ED treatment centers could face implementation challenges due to several barriers [66], including financial constraints and management challenges on the organizational level. In order to address these issues, regular communication strategies and facilitation of the implementation processes are key. In light of this objective, we aim to organize regular meetings and we will establish consistent communication lines, both online and on-site. Newsletters are prepared regularly in order to convey important updates and to optimize the overall sense of community among our participating partners.

Third, completion of all measurements may require substantial efforts from participants. Given the number of relevant questionnaires being administered, a full measurement may take up to two hours to complete. Although encouraging visuals will be implemented digitally to facilitate completion of each measurement over an extended time span with regular breaks, completing all measurements in time may still be challenging for participants. If possible, completion of measurements will be supported on-site at the institutions.

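### The 90% power for the primary outcome assumes almost complete T1 EDE-Q data: 232 carries no attrition allowance, although the protocol itself expects dropout and incomplete data

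*Protocol article*

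**What the plan says.** The Sample size section of the protocol article gives the whole derivation. The inputs are "a two-tailed alpha of 5%, a power of 90% and a medium effect size of d = 0.50 is assumed". The first result follows: "This yields a sample size of 86 patients per treatment arm". Clustering in the group schema therapy (GST) arm is then added: "Assuming a group size of 8 participants and an intra-class correlation of 0.10, a design effect of 1.70 was computed". The section concludes that "the total number of necessary study participants is equal to *N* = 232". The Methods paragraph of the Abstract uses the same 232 as the recruitment target: "patients with a CBT-E referral will be recruited from five treatment centers".

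Three other places bear on loss. The Background reports that "CBT-E is characterized by a substantial dropout rate: 20–54% in randomized controlled trials", and says that patients without an early response, who are the trial population, "may be at an elevated risk of dropping out and achieving suboptimal clinical outcomes". Operational challenges says that "there is an inherent risk of incomplete data, which we aim to address by conducting all statistical analyses according to the intention-to-treat principles", and adds that a full measurement may take up to two hours.

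The Data analysis section defines intention-to-treat as analysis by assigned arm. Its Clinical effectiveness subsection plans a dropout analysis, missing value analysis, sensitivity analyses and suitable missing-data procedures.

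**The concern.** The number needed for 90% power and the number to be recruited are identical, so any loss of primary outcome data beyond rounding comes straight out of the power. The article does not treat loss as unlikely: it describes dropout as a main weakness of the control treatment and foresees gaps in the data.

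In Operational challenges, intention-to-treat is the analytic answer offered to incomplete data. That principle settles which patients are compared and in which arm. It does not supply a missing EDE-Q score.

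What is at stake is how a null result is read. A reader would credit the trial with a 10% type II error at d = 0.50. With 20% equal loss and an unadjusted comparison, that error would be 15–17%.

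**Working it through.** **Inputs from the Sample size section.** d = 0.50 (SD 1), two-sided alpha 0.05, power 90%, group size 8, intra-class correlation (ICC) 0.10, 86 in CBT-E and 146 in GST.

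**Reproducing 232.**
- A two-sample t-test with these inputs needs 85.03 per arm, rounded up to 86.
- Design effect: 1 + (8 − 1) × 0.10 = 1.70.
- GST arm: 86 × 1.70 = 146.2, taken as 146.
- Total: 146 + 86 = 232.

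The stated figure is reached with no loss term.

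**Power with loss.** Let f be the fraction of randomised patients without a T1 EDE-Q, equal in both arms.
- CBT-E: n_C = 86(1 − f).
- GST, effective: n_G = 146(1 − f)/DE.
- Noncentrality: 0.50 / √(1/n_C + 1/n_G), with n_C + n_G − 2 degrees of freedom (noncentral t).

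The design effect (DE) is taken two ways: held at 1.70, or reduced as missing patients shrink the analysed groups, DE = 1 + (8(1 − f) − 1) × 0.10.

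Example at f = 0.20:
- n_C = 68.8 and the GST count is 116.8.
- DE 1.70: n_G = 68.7, noncentrality 0.50/0.1706 = 2.93, power 82.9%.
- DE 1 + 5.4 × 0.10 = 1.54: n_G = 75.8, noncentrality 0.50/0.1665 = 3.00, power 84.7%.

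| Loss, both arms | DE fixed at 1.70 | DE shrinking |
|---|---|---|
| 0% | 90.3% | 90.3% |
| 1% | 90.0% | 90.1% |
| 2% | 89.7% | 89.9% |
| 10% | 87.1% | 87.8% |
| 20% | 82.9% | 84.7% |
| 30% | 77.6% | 80.6% |
| 54% | 59.3% | 65.3% |

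The slack is about 1% by the t calculation. A normal approximation still gives just over 90% at 2%.

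**Loss in the CBT-E arm only.** With GST complete (n_G = 146/1.70 = 85.9), power is 86.7% at 20% loss and 73.3% at 54%.

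**Possible gain from baseline adjustment.** If the model conditions on the pre-randomisation EDE-Q with baseline–T1 correlation r, the variance is multiplied by 1 − r². At 20% equal loss and r = 0.4 the factor is 0.84 and power is 89–90%. At 54% loss, r would have to be about 0.68–0.73 to restore 90% (normal approximation). These correlations are assumptions, because the article gives none.

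**What is assumed.** The values of f are illustrative. All figures take 86:146 as randomised, following the Sample size section.

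**The case against.** The strongest reply is that the article gives no rate for missing T1 EDE-Q, and that 20–54% is a poor stand-in for one. That range is dropout from CBT-E treatment in earlier trials. Here patients are randomised only after eight sessions and a second EDE-Q, so those lost during phase 1 never enter the randomised sample. Stopping treatment is not leaving the study: patients are withdrawn only at their own request, and T1 is tied to the known treatment end date. The range describes CBT-E, whereas the Background suggests that GST may prevent dropout and the Objectives hypothesise better adherence with it. All of this stands. A reader might infer that the protocol's own figures put power at 59–65%. They do not: 54% is an upper marker and not a forecast.

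A reader might also infer that power must fall clearly short even at moderate loss. The planned analysis is a mixed model that accounts for correlation between time points, and the EDE-Q is measured twice before randomisation. A correlation near 0.4 would roughly restore 90% at 20% loss. However, the Sample size section claims no such gain and states no correlation, so this is a possible defence and not one the article makes.

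Nor do the documents support adding a diluted treatment effect on top of the loss. Nothing says that d = 0.50 is an effect in completers, and it may already be the intention-to-treat effect.

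Finally, intention-to-treat is not the only provision for incomplete data. The Data analysis section plans missing-data procedures, and Operational challenges adds tailored leaflets and on-site support. Its sentence on intention-to-treat makes no claim about power; the wording is loose. None of this alters the fact that 232 contains no allowance.

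**Conclusion.** The point holds in limited form. The arithmetic behind 232 is correct. What is wrong is that 90% power is stated without the condition it depends on, namely T1 EDE-Q data complete to within about 1–2%, in a document that expects dropout and incomplete data. Because every step of the derivation is shown and ends at the recruitment target, an attrition step cannot simply have been left out of a condensed article: it would have produced a number other than 232.

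The absence of an allowance is certain; the size of the shortfall is conditional. For an unadjusted comparison with equal loss, power is about 87–88% at 10%, 83–85% at 20% and 78–81% at 30%; with 20% loss in CBT-E only, it is 87%. These values rest on assumed loss rates and on taking no credit for baseline adjustment. It would go too far to say that every single patient must be measured, since about 1% loss still leaves 90%. Allocation and the choice of primary outcome are not affected. This is a should-fix.

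**What to change.** In the Sample size section:
1. State that 90% power applies to 232 patients with an analysable T1 EDE-Q.
2. State and justify an expected T1 loss for each arm, distinguishing missing outcome data from stopping treatment.
3. Give the power delivered when 232 are randomised under that loss.
4. If adjustment for the pre-randomisation EDE-Q is relied on to recover power, say so and state the assumed correlation.

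In Operational challenges, replace the statement that intention-to-treat addresses incomplete data with a reference to the missing-data procedures in the Clinical effectiveness part of Data analysis, noting that these do not fully restore lost information.

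The cost is a few sentences and a stated power that is probably less favourable. Correcting the statement requires no extra enrolment. If the sponsor prefers to keep 90% by randomising more, inflating each arm by 1/(1 − f) with DE at 1.70 gives 108 + 183 = 291 at 20% loss. If analysed groups shrink, the figure is 108 + 166 = 274.
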